### Strategies to improve adherence to the interventions {11c}

Adherence of participants to the two intervention conditions is enhanced through regular contact with their personal PA coach. Additionally, the smart ring and accompanying mobile app facilitate self-monitoring of PA behavior and thereby promote daily engagement with health-related metrics. Monitoring of adherence to the intervention conditions is achieved through documentation of smart ring data and coaching session contents by the PA coaches.

Participants of all three groups (CG, IG1, and IG2) receive written feedback on cardiorespiratory fitness, PA level, and body composition after each data assessment (T0, T1, T2). This feedback includes graphical visualization with comparison over time and may increase self-awareness, perceived progress, and motivation.

### Relevant concomitant care permitted or prohibited during the trial {11d}

All study participants follow treatment as usual in the day clinic. Apart from this, there are no requirements or restrictions on concomitant other treatments.

### Provisions for posttrial care {30}

In the event of study-related damage or injuries, the liability of the University of Basel, Medical Faculty, provides compensation, except for claims that arise from misconduct or gross negligence.

## Outcomes {12}

### Primary outcome

#### Device-based PA

The primary outcome is the change in device-measured PA over time, measured using a Fibion® SENS device (Fibion Inc., Jyväskylä, Finland) over 7 consecutive days at the three timepoints. The device is attached to the anterior thigh (centerline, one-third from the distal end) and sealed in a waterproof covering with medical adhesive tape. Participants wear it continuously, 24 h/day, facilitated by its low-maintenance design (no charging required). The sensor records raw triaxial acceleration at 12.5 Hz and classifies PA type (sitting, long sitting, standing, walking, cycling) and intensity (light [LPA], moderate [MPA], vigorous [VPA]) with high accuracy [103]. Reliability and validity have been demonstrated in previous research [104–109]. To enhance data accuracy, participants record their bedtime, ensuring that sleep periods are excluded from analysis to prevent an overestimation of sedentary time. At the end of the 7-day period, participants remove adhesive tape and return the Fibion® SENS device at the day clinic.

### Secondary outcomes

#### Self-reported physical activity

The 7-Day Physical Activity Recall (7DPAR) is used to assess participants’ self-reported PA through a structured 20-min interview by a trained research assistant [110–112]. The 7DPAR assesses all PA bouts of at least 10-min duration over the past 7 days. For a PA bout to be recorded, intensity needs to be at least moderate [112]. Interviewers record breaks during PA, which are subtracted from total durations. In addition to total minutes of PA in moderate, moderate to vigorous, and vigorous intensity per week, the 7DPAR also captures strength and flexibility training. As part of this study, the 7DPAR is supplemented by a question on participation in structured exercise and sports programs. This latter component is particularly relevant, as the coaching intervention aims to support engagement in such programs [113].

#### Depressive symptom severity

Depression severity is assessed using the Hamilton Depression Rating Scale (HAMD-17) [114] and the self-report Beck Depression Inventory-II (BDI-II) [115, 116]. The HAMD-17 is administered as a structured clinical interview by trained study personnel. The BDI-II is a 21-item questionnaire that assesses affective, behavioral, cognitive, and somatic symptoms of unipolar depression. Total scores range from 0 to 52 for the HAMD-17 and from 0 to 63 for the BDI-II, with higher scores indicating greater depression severity. Both instruments demonstrate acceptable reliability and validity [117–119]. Treatment response is defined as a ≥ 50% reduction in HAMD-17 score from baseline to endpoint, partial response as a 25%–49% reduction, and nonresponse as a < 25% reduction. Remission is defined as a HAMD score ≤ 7 [120]. For the BDI-II, response is similarly defined as a ≥ 50% reduction and remission as a score ≤ 9; no consensus definitions exist for partial response [121]. According to the German S3 clinical guidelines [122], HAMD-17 scores ≥ 17 indicate at least moderate depression, whereas a BDI-II score of ≥ 20 reflects moderate symptom severity [123, 124].

#### Health-related quality of life

The Medical Outcomes Study 12-Item Short-Form Health Survey (SF-12) is used to assess participants’ self-perceived health [125]. As one of the most widely applied instruments in population health research [126], the SF-12 has well-documented reliability and validity [127, 128]. Composite scores for physical and psychological health are calculated according to the SF-12 scoring manual, with higher scores indicating better health functioning. To our knowledge, no minimal clinically important difference (MCID) data specific to patients with MDD are currently available; therefore, we reference MCID values identified in patients with low back pain, where improvements of > 3.77 points in the psychological subscale and > 3.29 points in the physical subscale have been established [129].

#### Social-cognitive and affective determinants

To evaluate the effectiveness of the theory-based coaching intervention in influencing the targeted psychological mechanisms, a range of social-cognitive (reflective) and affective determinants are assessed.

##### Exercise-related self-efficacy

Exercise-related self-efficacy is assessed using three items measuring confidence in initiating, maintaining, and resuming exercise after a relapse (e.g., “I feel confident to start a new exercise activity”). This scale has demonstrated acceptable psychometric properties [130] and has been used in previous intervention studies [131–133]. Responses range from 0 (not at all confident) to 5 (completely confident), with the total score calculated as the sum of all three items. There are currently no established MCID scores for this index.

##### Exercise-related outcome expectations

Outcome expectancies are assessed using nine positively framed (“pros”) (e.g., “Regular exercise improves my physical appearance”) and seven negatively framed (“cons”) items (e.g., “Exercise puts me in situations where I feel embarrassed”) [134]. Items are rated on a 4-point Likert scale from 1 (not true) to 4 (completely true). The scale has demonstrated satisfactory psychometric properties [134]. Composite scores for positive and negative expectancies are calculated as the arithmetic means of their respective items. There are currently no established MCID scores for this index.

##### Exercise intention

Exercise-related goal intentions are assessed using a single item measuring the strength of participants’ intention to exercise regularly over the coming weeks and months (0 = no intention, 5 = very strong intention) [130]. This measure has demonstrated acceptable reliability and validity in previous studies [135, 136]. There are currently no established MCID scores for this index.

##### Exercise-related self-concordance

Exercise-related self-concordance is assessed using the 12-item SSK scale [135], based on the self-concordance model by Sheldon and Elliot [137]. The scale comprises four subscales measuring intrinsic (e.g., “I exercise because it’s fun for me”), identified (e.g., “I exercise because I have good reasons to be physically active”), introjected (e.g., “I exercise because otherwise I would feel guilty”), and extrinsic (e.g., “I exercise because others tell me to”) motivations for exercising. Items are rated on a 6-point Likert scale (1 = not at all true, 6 = completely true). An overall self-concordance index is calculated by summing the intrinsic and identified mean scores and subtracting the introjected and extrinsic mean scores. The SSK scale has demonstrated satisfactory reliability and validity [135]. There are currently no established MCID scores for this index.

##### Exercise-related action planning

Action planning is assessed using a 5-item index with established reliability and validity [137, 138], measuring the extent to which participants have pre-planned their exercise participation. Specifically, participants are asked about their planning regarding when, where, how, how often, and with whom they exercise. Responses are rated on a 4-point scale (1 = not at all true, 4 = completely true), and item scores are summed to create an overall index. There are currently no established MCID scores for this index.

##### Perceived barriers to exercise

Perceived exercise-related barriers are assessed using a 19-item scale that identifies various obstacles to regular exercise participation [139]. The instrument has demonstrated satisfactory psychometric properties [54, 139]. Participants rate how often they perceive each barrier (e.g., “I have too much work to do”) on a 4-point Likert scale (1 = almost never, 4 = almost always). The mean score is calculated to provide a single overall score. There are currently no established MCID scores for this index.

##### Exercise-related coping planning

Exercise-related coping planning is assessed using a 5-item index [138]. Participants are asked to what extent they use self-regulation strategies to overcome potential barriers to exercise (e.g., “I have made a detailed plan for what to do in difficult situations to act according to my intentions”). Responses are rated on a 4-point scale (1 = not at all true, 4 = completely true). Item scores are summed to create a composite index. The scale’s reliability and validity have been established in previous research [136, 138]. There are currently no established MCID scores for this index.

##### Exercise-related social support

Social support for exercise is assessed using a 7-item index [134], focusing on support from relevant others (e.g., “Close family or friends help me plan my exercise”). Responses are given on a 4-point Likert scale (1 = almost never, 4 = almost always). Item scores are summed to create a composite index. The scale has demonstrated psychometric soundness in previous studies [133, 134]. There are currently no established MCID scores for this index.

##### Explicit affective attitudes towards exercise

Participants’ affective evaluations of past exercise experiences are assessed using the Affective Exercise Experiences questionnaire (AFFEXX), a 36-item instrument developed to capture explicit affective attitudes toward exercise [66]. The AFFEXX includes 10 subscales, organized into 3 overarching domains: (1) antecedent cognitive appraisals, (2) core affective exercise experiences, and (3) attraction vs. antipathy as a motivational outcome. The antecedent cognitive appraisal domain comprises six subscales that assess constructs such as competence-incompetence, interest-boredom, and pride/honor-shame/guilt. These cognitive appraisals are theorized to shape the core affective exercise experience, which includes three subscales: pleasure-displeasure, energy-tiredness, and calmness-tension. In turn, these affective responses are assumed to influence the motivational outcome, assessed via a single subscale capturing the degree to which exercise is experienced as attractive or aversive. Each of the 36 items presents a pair of bipolar statements, and participants rate the extent to which their views and experiences align with either pole using a 7-point Likert scale (1 = perfectly matching left statement, 7 = perfectly matching right statement). Scoring is performed using the official scoring script provided by the questionnaire developers [140]. Reverse-coded items are recoded before calculating subscale scores. Each of the 10 subscales is scored independently. In addition, composite scores are calculated for the domains of antecedent cognitive appraisals (sum of six subscales) and core affective experiences (sum of three subscales). The validity of this instrument has been documented in previous research [66, 141]. The MCID for this instrument has not been determined yet.

##### Implicit attitudes towards exercise

Automatic affective evaluations of exercise are assessed by using the Single Target Implicit Association Test (ST-IAT), administered via E-Prime 2.0 (Psychological Software Tools, USA). Unlike standard IATs, which compare associations between evaluative concepts (e.g., “good” vs. “bad” and “physical activity” vs. “physical inactivity”), the ST-IAT assesses attitudes toward a single target concept — exercise — without a direct comparison. The ST-IAT employed in this study has shown reliability and discriminant validity [142]. In this version, “exercise” serves as the target concept, while “good” and “bad” are the evaluative categories. The target stimuli are photographs of middle-aged adults engaging in exercise activities (e.g., swimming, running), and these images show individuals without emotional expressions (e.g., no smiling or pained faces). Rather than using attribute words, emoticons (eight smileys and eight frownies) are used, which reduces potential confounds related to verbal abilities and ensures visual stimulus consistency [143]. The task consists of 2 phases: The first phase includes 16 practice trials, where participants categorize emoticons as either “good” or “bad.” The second phase consists of two blocks, where participants assign emoticons and target images to the “exercise-good” or “exercise-bad” categories. The order of the blocks is counterbalanced across participants, and after the first block, the assignment of exercise to the evaluative categories is reversed. Each block includes 32 trials, preceded by 16 practice trials to minimize learning effects. Inaccurate responses are repeated until a correct response is recorded. Response speed and accuracy are emphasized, with participants responding using their left or right index finger. The primary dependent variable is the D-score, calculated by dividing the difference in mean reaction time between the two blocks by the within-individual standard deviation of reaction times across compatible and incompatible trials [144]. The D-score ranges from −2 to +2, with |0.15|, |0.35|, and |0.64| indicating slight, moderate, and strong preference (or aversion), respectively [145].

##### Physical self-perception

Physical self-perception is assessed using the Physical Self-Description Questionnaire (PSDQ), a self-report tool designed to evaluate various dimensions of physical self-concept [146]. In this study, we focus on 4 subscales: endurance, flexibility, coordination, and strength, comprising a total of 14 items. Each item presents a statement that participants rate according to their level of agreement or disagreement. Subscale scores are calculated by averaging the responses to the items within each subscale, with higher scores indicating more positive self-perceptions in the respective areas. Extensive psychometric evaluation of the PSDQ indicates that it is a reliable and valid instrument [147–149].

### Potential moderators

#### Body mass index, percentage of body fat, and waist circumference

Body weight is measured using a digital scale (BC-545, Tanita, USA), without shoes and to the nearest 0.1 kg, with participants in light clothing. Height is measured using a stadiometer, with participants standing barefoot, to the nearest 0.5 cm. BMI is calculated using the formula: weight (kg)/height^2^ (m^2^). According to WHO standards [150], participants are classified as overweight with a BMI ≥ 25.0 kg/m^2^ and obese with a BMI ≥ 30.0 kg/m^2^. A 5% weight loss is considered as the MCID for those classified as overweight or obese [151]. The BC-545 scale also performs bioelectrical impedance analysis, measuring body fat percentage. For healthy body fat, the WHO [150] recommends a maximum of 32% for women and 25% for men. A 2% reduction in body fat percentage is defined as the MCID [152]. Waist circumference is measured using a flexible tape at the natural waist (midway between the ribcage and iliac crest). According to the National Cholesterol Education Program [153]^153^, a waist circumference ≥ 80 cm for women and ≥ 94 cm for men turned out to be a risk factor for metabolic syndrome.

#### Cardiorespiratory fitness

Cardiorespiratory fitness is considered a potential moderator to determine whether the effectiveness of the intervention is influenced by participants’ initial fitness levels. This is supported by previous research indicating that the effects of an affect-based exercise prescription were moderated by cardiorespiratory fitness levels [154]. To assess cardiorespiratory fitness, we use the Åstrand indirect test of maximal oxygen uptake (VO_2_max) [155], performed on a bicycle ergometer (Ergoselect 200), which is validated for measuring submaximal fitness [155]. Gender- and age-adjusted cutoffs categorize participants into low, moderate, and high fitness groups [155]. The reliability and validity of the Åstrand nomogram and its linear extrapolation for deriving VO_2_max have been well documented [156]. A submaximal fitness test is employed, as more than half of individuals with depression do not meet the primary or secondary criteria for maximal exertion in cardiopulmonary exercise testing [157].

#### Medical history

Psychiatric medical history is assessed as a potential moderator. Using a structured questionnaire, participants provide information on current and past depressive episodes, treatments—including medication use—and comorbid diagnoses.

#### Sociodemographic background

Sociodemographic background is assessed through a structured questionnaire. Participants provide information on their age, mother tongue, nationality, relationship status, educational background, work experience, the presence of children in the household, smoking status, and household income.

### Implementation evaluation

#### Reach, dose, fidelity, and adaptation

To comprehensively assess the intervention’s effectiveness, its implementation is systematically analyzed. This evaluation follows the framework proposed by the Medical Research Council (MRC) [158], which has been previously applied for the implementation evaluation of a PA counselling in in-patients with MDD [159] to assess implementation processes. Specifically, four key components are examined: (1) Reach—assessing whether the intervention successfully engages the intended target group; (2) dose—evaluating the duration and number of administered intervention sessions; (3) fidelity—determining adherence to the prescribed administration protocol; and (4) adaptation—identifying any modifications made to the intervention protocol.

The above-described analyses are based on quantitative data collected from coaches. Thus, coaches document key aspects of their sessions using a standardized tool. This documentation includes session dates, preparation time, coaching duration, follow-up time, the Feeling Scale (FS) [89], Felt Arousal Scale (FAS) [90] and Borg Perceived Exertion Scale (Borg) [91], and session content, e.g., BCTs employed.

#### Participant satisfaction

Additionally, participant satisfaction data are gathered via questionnaires administered at post-intervention (T1: IG1 and IG2) and follow-up (T2: IG2). The questionnaire, adapted from a previous project [159], assesses participants’ expectations, comprehension of coaching content, satisfaction with the coach, motivation to continue, likelihood of recommending the intervention, perceived suitability for promoting PA, overall satisfaction, and perceived effort in relation to outcomes. Responses are recorded on a 4-point Likert scale (ranging from “no” to “yes”), while perceived effort is assessed using a scale from “too high” to “low.” Additionally, participants report their perceptions of coaching session intervals, with response options ranging from “too long” to “too short.”

### Participant timeline {13}

Patients are screened within their first week of admission to the day clinic and invited to participate in the study. Interested individuals receive detailed study information from designated study personnel. Recruitment continues until 114 participants have been enrolled. Following informed consent, baseline assessments are initiated promptly. As the 10-week intervention is designed to run concurrently with the 12-week standard treatment in the day clinic, timely initiation of baseline assessments is ensured. The participant timeline is illustrated schematically in Table 1.

**Table 1 Tab1:**
[figure not shown]
Schematic illustration of participant timeline in accordance with SPIRIT guidelines

### Sample size {14}

Based on the expectation of a weak-to-moderate effect size (*f* = 0.175) for the primary outcome of change in device-based PA, an alpha error probability of 0.05, and a correlation between repeated measures of *r* = 0.50, 29 participants per group (87 in total) are required to achieve 90% power via ANOVA (G*Power 3.1.9.7). The assumed effect size was informed by previously published comparable RCTs [160, 161]. The final sample size is increased by 30% (*N* = 114) to account for anticipated attrition, defined as loss to follow-up with missing primary outcome data. This adjustment aligns with a previously published RCT involving in-patients receiving PA counselling, which reported a dropout rate of 30% [162].

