## Trial design {8}

This study is a single-center, three-arm randomized controlled trial (RCT) with an allocation ratio of 1:1:1. It includes two intervention groups (IG1, IG2) and one control group (CG) and follows an open-label design. The trial is conducted in collaboration between the Sonnenhalde AG Psychiatric Clinic, Riehen, Switzerland, and the Department of Sport, Exercise and Health (DSBG) at the University of Basel, Basel, Switzerland.

The intervention is delivered in an outpatient setting, recruiting patients from day clinics of the Sonnenhalde AG. Assessments are conducted at three time points: (a) baseline (T0), (b) post-intervention (T1, 10 weeks after baseline), and (c) follow-up (T2, 36 weeks after baseline). The follow-up period of 26 weeks after post-intervention ensures alignment with prior comparable studies [77–79]. All assessments are conducted on-site at the day clinics.

An overview of the study design is provided in Fig. 1. The protocol is designed in accordance with the SPIRIT 2025 statement for interventional trials [80].

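### Adding 30% to 87 does not offset a 30% loss: 114 randomised leaves about 80 with primary outcome data, not the 87 needed for 90% power

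*Protocol article*

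**What the plan says.** All the relevant figures are in the protocol article, Sample size {14}.

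- The power statement is that "29 participants per group (87 in total) are required to achieve 90% power via ANOVA". Its inputs are f = 0.175, "an alpha error probability of 0.05" and "a correlation between repeated measures of *r* = 0.50".
- The attrition step follows: "The final sample size is increased by 30" percent, giving N = 114. Attrition is defined there as loss to follow-up with the primary outcome missing.
- The justification is that the allowance matches an earlier trial of physical activity counselling in in-patients, "which reported a dropout rate of 30" percent.

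Participant timeline {13} stops recruitment at 114. The Abstract and the text with Fig. 1 under Trial design {8} repeat that number. No section gives a planned loss other than 30%.

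**The concern.** The section treats 87 as the number needed with primary outcome data and 30% as the expected proportion without it. The randomised number should then satisfy N × (1 − 0.30) ≥ 87, which means dividing 87 by 0.70. The figure of 114 comes from multiplying 87 by 1.30. The two operations differ because the 30% is lost from the larger randomised number, not from the 87 who have to remain.

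At stake is the relation between three figures that the results report is likely to repeat: 114 randomised, 30% attrition and 90% power. If attrition is as planned, the trial has fewer evaluable participants than its own calculation requires, even if the effect size and correlation assumptions are exactly right.

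**Working it through.** **Inputs**

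| Quantity | Value | Source |
|---|---|---|
| Effect size f | 0.175 | Sample size {14} |
| Alpha | 0.05 | Sample size {14} |
| Correlation ρ | 0.50 | Sample size {14} |
| Groups k | 3, allocated 1:1:1 | Trial design {8} |
| Measurements m | 3 (T0, T1, T2) | Trial design {8} |
| Required N | 87 (29 per group) | Sample size {14} |
| Attrition | 30% | Sample size {14} |
| Randomised N | 114 | Sample size {14} |
| Test and ε | within-between interaction, ε = 1 | assumed; the section says only ANOVA |

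**Step 1. Reproduce the 87.** For the repeated-measures within-between interaction in G*Power:

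- λ = f² · N · m / (1 − ρ) = 0.030625 × 3 / 0.50 × N = 0.18375 · N
- df₁ = (k − 1)(m − 1) = 4
- df₂ = (N − k)(m − 1) = 2(N − 3)

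At N = 87, λ = 15.99 and df₂ = 168, and power is 0.903. This is the smallest N that reaches 90%, so the stated 87 is reproduced. The other variants tried do not give 87 at 90% power: the interaction with two measurements needs 108, the within factor 72 (m = 3) or 90 (m = 2), the between factor 279 or 315, and a one-way ANOVA 417.

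**Step 2. Reproduce the 114.**

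- Multiplying: 87 × 1.30 = 113.1, rounded up to 114. Per arm, 29 × 1.30 = 37.7, rounded up to 38, and 3 × 38 = 114.
- Dividing: 87 / 0.70 = 124.3, rounded up to 125. Per arm, 29 / 0.70 = 41.4, rounded up to 42, and 3 × 42 = 126.

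Only multiplication gives 114.

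**Step 3. What 114 leaves.**

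- At 30% loss: 114 × 0.70 = 79.8 in total, or 26.6 per arm. The shortfall is 87 − 79.8 = 7.2.
- Largest loss that still leaves 87: (114 − 87) / 114 = 27 / 114 = 23.7%.

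**Step 4. Power on the same formula.**

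| Evaluable N | Power |
|---|---|
| 78 | 0.863 |
| 79.8 | 0.872 |
| 80 | 0.873 |
| 81 | 0.878 |
| 87 | 0.903 |

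At the planned loss, power is about 87%, some 3 percentage points below the stated 90%.

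**The case against.** The strongest reply has four parts.

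1. **The sentence is literally true.** The size was increased by about 30%, and the section nowhere states outright that 87 will remain after a 30% loss. That is right as far as it goes. But the section gives covering anticipated attrition as the purpose of the increase and a 30% dropout rate as its justification. The only natural reading is that 114 is meant to absorb a 30% loss.

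2. **The 30% may not be a rate of missing outcome data.** The earlier trial is described only as having a dropout rate, and the section on retention {18b} keeps inviting people who stop the intervention to the assessments. Actual missing outcome data could therefore be below 30%, and the shortfall arises only if the loss exceeds 23.7%. This stands as a condition on the consequence. It does not repair the calculation, because the section adopts 30% as its allowance for attrition, which it defines as missing primary outcome data.

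3. **The primary analysis is not a complete-case analysis.** The statistical methods {20a} use a linear mixed model with T1 and T2 as outcomes, and {20c} sets intention-to-treat with imputation. A participant with T1 but no T2 still contributes information, so a count of 80 may understate what the analysis holds. This also stands. However, the sample size calculation takes no credit for partial data, and imputation does not restore lost participants in it.

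4. **The loss is small.** Three points of power is little beside the uncertainty in f = 0.175 and ρ = 0.50. This is fair about the consequence, but it does not make the stated figures consistent.

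**Conclusion.** The concern holds. On the section's own inputs, 114 randomised with 30% loss gives about 80 participants with primary outcome data, against the 87 required. N = 114 covers attrition only up to 23.7%.

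The attrition arithmetic needs nothing beyond 87, 114 and 30%. The power figure of about 87% also assumes a 3 × 3 within-between interaction test with ε = 1. The protocol does not name that test; it is inferred because it returns exactly 87 at 90% power and the alternatives tried do not. It is also not the planned primary analysis, which adjusts for baseline and compares each intervention group with control using Dunnett's adjustment. The 87% therefore corrects the protocol's own calculation and does not estimate the power of the planned model.

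The practical effect is modest: about 7 participants and 3 points of power. It still needs correcting, because a sample size and power statement that others will rely on does not follow from its inputs.

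**What to change.** Restate the attrition step in Sample size {14} along these lines:

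> With 114 randomised, 87 participants have primary outcome data, giving 90% power, if attrition is at most 23.7%. At 30% attrition about 80 have primary outcome data, and power on the same calculation is about 87%.

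Name the ANOVA test and the ε used beside the power figures, so that they are not read as applying to the mixed model.

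The cost is one reworded paragraph and a stated power about 3 points less favourable at 30% loss. No extra participants are needed, and the design and analysis do not change.

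If the sponsor prefers to keep 90% power at 30% loss, the randomised number becomes 125, or 126 with equal arms (125 × 0.70 = 87.5; 126 × 0.70 = 88.2). That is 11 or 12 more participants, about 8 more weeks at the 1.5 per week projected under Recruitment {15} (12 / 1.5 = 8). The figure of 114 would then also have to change in the Abstract, in the text with Fig. 1 and in Participant timeline {13}.
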